### Interventions

Participants will visit the laboratory (located in the Smart-Aging Research Center) for two sessions, one week apart, corresponding to the two intervention conditions. In both sessions, the participants sit comfortably on a stool with their feet firmly resting on the ground and their arms relaxed by their sides. They have to wear the Oculus visor (oculus.com), equipped with two lenses that show the virtual world. They will be instructed to keep their bodies still but they can move and rotate their head, to explore the virtual body and the environment. The virtual environment, as well as the virtual bodies and the animations, is modelled in 3D Studio Max 2015 and implemented in Unity3D: it represents an open space with a green floor (simulating a meadow) and a natural-looking illuminated sky, with a visible horizon. Participants will see a gender-matched life-sized humanoid virtual body.

The intervention will be performed in two conditions. The experimental intervention displays the virtual body in 1PP, where the virtual body substitutes and is spatially coincident with the real one; in other words, to observe the virtual body, the participant has to look towards him/herself. The control intervention consists of displaying the same virtual body in 3PP, where the virtual body is collocated approximately 1.5 m to the left of the real participant’s body; in other words, to observe the virtual body, the participant has to rotate his head and look towards his left side.

In both conditions (1PP and 3PP), the intervention starts with a familiarization phase of 4 min (hereinafter baseline) where the gender-matched virtual body is displayed but there is no animation yet (i.e. the virtual body in both 1PP or 3PP is standing still). This phase is necessary to induce the illusory sensation of ownership over the virtual body (in 1PP) or not to induce it (in 3PP) (see the “Measurements” section for the online questionnaire on SoBO and SoA) for the baseline recording of the HR (see the “Measurements” section) and to check for eventual sickness problems due to the virtual display.

After that, the actual intervention consists of a vHIE performed by the virtual body exclusively: while seated, participants will see the virtual body (either in 1PP or 3PP) alternating 30 s of running and 30 s of slow walking, for a total of 8 min [17, 33]. After that, we will ask the participant to stay still and close his/her eyes, while we still record an extra 30 s of the HR (see the “Measurements” section) (see Fig. 2b). While the slow walking animation will be the same for all participants, in order to choose the speed of the running animation, after the familiarization phase, we will show four different options on the virtual body and individuals verbally report which one is subjectively perceived as considerably fast but feasible. This is necessary to maximize the possibility of having an actual physiological activation but, at the same time, to display an animation that is subjectively plausible so as to not break the illusion of ownership in 1PP.

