**Fig. 2 Fig2:**
[figure not shown]
General procedure of the study. **a** The protocol of one experimental session (in both sessions the procedure is the same, the intervention condition changes) with its timeline. The first part describes the measurements before the intervention (TDMS and Stroop task with fNIRS recording); the central part corresponds to the vHIE intervention (that, according to the session, may be in 1PP or 3PP). **b** The intervention details: every 30 s, the speed of the avatar changes from slow walking to running; at specific timepoints, we will administer the online questionnaire for SoBO and SoA. The third part of A. describes the measurements after the intervention (same as before the intervention)

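### Running speed appears to be chosen afresh in each session, after exposure to that session's perspective, so avatar speed may differ between 1PP and 3PP and a difference could not be credited to perspective alone

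*Protocol article*

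**What the plan says.** All references are to the protocol article.

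- **Interventions, sessions.** Participants attend "two sessions, one week apart, corresponding to the two intervention conditions".
- **Interventions, familiarization.** "In both conditions (1PP and 3PP), the intervention starts with a familiarization phase of 4 min", with the avatar standing still. Its purpose depends on the condition: "This phase is necessary to induce the illusory sensation of ownership over the virtual body (in 1PP) or not to induce it (in 3PP").
- **Interventions, speed.** The running speed is set next: "after the familiarization phase, we will show four different options on the virtual body and individuals verbally report which one is subjectively perceived" as fast yet achievable. The stated motive is "This is necessary to maximize the possibility of having an actual physiological activation", together with keeping the animation believable enough not to break ownership in 1PP.
- **Interventions, what is fixed.** "While the slow walking animation will be the same for all participants". No matching statement is made for running, either between participants or between one participant's two sessions.
- **Fig. 2 legend.** "in both sessions the procedure is the same, the intervention condition changes".
- **Discussion.** The two conditions are described as the same virtual exercise shown from two viewpoints.
- **Primary outcomes; Stroop task's RT and ER; Heart rate data.** 1PP versus 3PP is named as the main comparison. The Stroop analysis is a TIME by CONDITION repeated-measures ANOVA. The heart-rate check predicts that the running change from baseline (dHRr) in 1PP exceeds every other measurement.

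**The concern.** The cross-over isolates perspective only if a participant receives the same stimulus in both sessions apart from the viewpoint. Here one component, running speed, is chosen after the condition has been assigned and after a phase meant to create ownership in one condition and withhold it in the other. What seems fast but achievable may well be judged differently for a body felt as one's own than for a body seen about 1.5 m away.

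The protocol itself treats speed as active, because it is tuned to produce physiological activation. Two things are at stake. One is how a 1PP–3PP difference in the Stroop and fNIRS outcomes is interpreted. The other is the heart-rate check, which is used in the first analysis phase to confirm that the illusion worked.

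**Working it through.** The point does not rest on a figure in the plan; the document gives no speed data. The check has three steps.

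**1. Is the speed chosen once or twice?**

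- One condition per session, two sessions (Interventions).
- Familiarization in each condition (Interventions).
- Speed chosen after the familiarization, on the displayed virtual body (Interventions).
- Same procedure in both sessions (Fig. 2 legend).

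Together these give one choice per session, made under that session's perspective. No sentence carries the first choice forward or matches the two. The Discussion's description of a single exercise is the only text pointing the other way.

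**2. What would an unequal choice do?**

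Let s be the effect of one speed step on the within-person contrast, p₊ the share choosing one step faster in 1PP than in 3PP, and p₋ the share choosing one step slower. Then

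bias in (1PP − 3PP) = s × (p₊ − p₋).

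- If choices change equally often in both directions, p₊ = p₋ and the bias is zero; only noise is added.
- If they lean one way, the bias does not shrink with n. It also does not cancel over the 15/15 order, because it follows CONDITION and not session number.
- For heart rate, the walking animation is common to all. A faster running animation in 1PP would mainly raise dHRr in 1PP, which is the pattern the protocol would read as proof of embodiment.

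**3. How much could it matter? (illustration only)**

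In a 2 × 2 within-subject ANOVA, the TIME by CONDITION test equals a paired t test on (after − before in 1PP) − (after − before in 3PP). Suppose perspective has no effect, but unequal speed shifts this contrast by dz standard deviations of itself. The test then has noncentrality dz × √n on n − 1 degrees of freedom. The dz values are assumptions. n = 28 and n = 30 are the calculated and recruited numbers under Sample size, and the test is two-sided at 0.05 (the protocol gives 0.05 without sidedness).

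| Assumed dz | dz × √28 | P(reject), n = 28 | dz × √30 | P(reject), n = 30 |
|---|---|---|---|---|
| 0 | 0 | 0.050 | 0 | 0.050 |
| 0.1 | 0.53 | 0.080 | 0.55 | 0.083 |
| 0.2 | 1.06 | 0.175 | 1.10 | 0.185 |
| 0.3 | 1.59 | 0.334 | 1.64 | 0.355 |
| 0.5 | 2.65 | 0.723 | 2.74 | 0.754 |

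A small shift does little; a shift of 0.2 to 0.3 would multiply the rate of false attribution to perspective several times. The document does not say where in this range, if anywhere, the trial lies.

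**The case against.** The strongest reply is that repetition of the choice is inferred. No sentence says outright that the speed is picked again in the second session, the same-procedure remark is a parenthesis in a figure legend, and the Discussion suggests one exercise per person. This stands as a limit on certainty. It does not remove the point, because the sections that describe the procedure all lead to a repeated choice and only a summary statement leads away from it.

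Second, choosing by the same rule in each perspective equates perceived intensity, whereas replaying one value equates physical speed. That is a respectable design. But the protocol does not claim it, and it does not fit the Discussion's claim that the exercise is the same.

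Third, a speed chosen because of the perspective is part of the condition as delivered, not a baseline confounder. The randomized contrast still estimates the effect of the whole package. This is correct, and it limits the harm to attribution: the package effect is estimable, the effect of perspective or ownership alone is not.

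Fourth, the published ANOVAs contain no speed term, but covariates and sensitivity analyses may sit in an analysis plan that is not shown. That absence is not held against the protocol.

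A reader might also infer that speed does differ, that the result is biased by a definite amount, or that every comparison in the trial is affected. The document supports none of these. It reports no choices, gives no effect per speed step and implies no direction. It also analyses before/after and running/walking factors, although 1PP versus 3PP is the only between-condition contrast.

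**Conclusion.** The point holds as a weakness in the stated procedure. As written, running speed can depend on the condition, and this conflicts with the premise that both conditions deliver the same exercise. If speeds lean one way, a Stroop, fNIRS or dHRr difference between 1PP and 3PP cannot be attributed to perspective alone, and neither the randomized order nor a larger sample cures that.

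The conclusion rests on the plain reading that the choice is made in each session, and on the protocol's own premise that speed affects the response. Size and direction are unknown, and the rejection rates in the table are conditional on assumed shifts. The change is worth making because it is cheap and protects the main contrast; it is not a demonstration that the trial is invalid.

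**What to change.** Reconcile Interventions and the Fig. 2 legend with the Discussion by stating that one running speed per participant is used in both sessions, and record the speed used in each.

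- **Preferred:** the participant chooses once, before the first session's familiarization, in a display that does not depend on the assigned perspective.
- **Otherwise:** the participant chooses in session 1, and the stored value is replayed in session 2.

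The cost is a sentence in the protocol and one stored value per person. The downside is that a fixed speed may feel slightly less plausible in one perspective. If the choice is made in session 1, this matters mainly for the 15 participants who start in 3PP, because they carry a speed chosen there into 1PP, where plausibility protects the illusion. In the other sequence the carried-over speed falls on 3PP, where no illusion is intended, so the balanced order does not offset this cost. That is the reason for preferring the perspective-neutral choice.

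For sessions already run (Trial status has recruitment from February to May 2019), report the chosen speed by condition, with the within-person difference. Treat any analysis that uses that difference, including one restricted to participants with equal speeds, as supportive only, since it conditions on something that arose after assignment. If the speed was in fact carried over, one sentence saying so settles the matter.

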### Measurements

#### Heart rate

During the interventions, in order to check if participants actually perceive the virtual body as their own (in 1PP and not in 3PP), we will record the HR with a Polar H10 HR monitor, controlled by a specific application via Bluetooth. Participants have to wear an elastic strip around the chest on which the HR monitor is attached, positioning it close to the heart, in order to record the HR for each intervention conditions (1PP and 3PP) during the baseline (4 min), the intervention (4 min running, 4 min slow walking, for a total of 8 min) plus an extra 30 s (where the participant is still with closed eyes) to check for eventual delay in the recording and to wait for the synchronization of the HR.

#### Online and offline questionnaires on SoBO and SoA

We will administer an online questionnaire for the subjective experience of SoBO and SoA. To control for eventual changes in subjective feelings during the intervention at different timepoints (in the middle of the baseline phase [i.e. after 2 min from the beginning if the IVR session], during the intervention at 1 min [i.e. while the avatar is running], at 2.5 min [i.e. while the avatar is slow walking ], at 5 min [i.e. while the avatar is running], and at 6.5 min [i.e. while the avatar is slow walking]), we will ask participants to rate their level of agreement (on a 1–7 Likert scale where 1 means “totally disagree” and 7 means “totally agree”) with respect to four statements: two of them (one is a “real statement” that checks for the actual presence of the illusion, while the other is a “control statement”) about SoBo and the other two about SoA (see Table 1) (see Fig. 2b).

**Table 1 Tab1:** Online questionnaire on SoBO and SoA

s1	SoBO	I feel as if I’m looking at my own body.
s2	SoBO control	I feel as if the virtual body belongs to another person.
s3	SoA	The virtual body moves just as I want, as if I am controlling it.
s4	SoA control	I feel as if the virtual body is controlling my will.

Questionnaire verbally administered during the vHIE (at 5 timepoints, at 2 min from baseline, and 1 min, 2.30, 5 and 6.30 min of vHIE) concerning the subjective participant’s feelings during the intervention. The statements s1 and s2 concern the SoBO, while the statements s3 and s4 concern the SoA. The statements s1 and s3 are “real statements” while statements s2 and s4 are “control statements.” Individuals will rate their level of agreement to the following statements on a 1–7 Likert scale (1 means “complete disagreement” and 7 means “complete agreement”).

Another questionnaire will be administered right after every IVR session (both after 1PP and 3PP intervention conditions) to check details for feelings of movement, motor control, and physical effort (see Table 2) (see Fig. 2 a). The statements are selected and adapted from previous studies [33, 41].

**Table 2 Tab2:** Offline questionnaire on SoBO and SoA

s5	Located	During the experiment, I felt as if my body was located where I saw the virtual body to be.
s6	Ownership	During the experiment, I felt that the virtual body was my own body.
s7	Standing	During the experiment, I felt that I was standing upright.
s8	My movements	During the experiment, I felt that the leg movements of the virtual body were my movements.
s9	Agency	During the experiment, I felt that the leg movements of the virtual body were caused by my movements.
s10	Ownership control	During the experiment, I felt that the virtual body belonged to someone else.
s11	Effort	I felt I had to give extra physical effort when the virtual body was walking faster.
s12	Vection	I felt that I was moving through space rather than the world moving past me.
s13	Walking	I felt that I was walking.
s14	Dragged	I felt that I was being dragged.
s16	Sliding	I felt that I was sliding.

Questionnaire self-administered after the vHIE interventions concerning the subjective participant’s feelings during the previous intervention. The underlying explored domains are listed in the first column (not shown to the participant) while the corresponding statements are listed in the second column. Individuals will rate their level of agreement to the following statements on a 1–7 Likert scale (1 means “complete disagreement” and 7 means “complete agreement”).

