### Randomization of interventions

The two intervention conditions will be administered to all participants in two separate sessions (one week apart). Random assignment to the first intervention using an online program (http://www.graphpad.com/quickcalcs/index.cfm) will take place [43]. Each participant is first assigned to a condition non-randomly (the random number generator is seeded with the time and the day). The assignment of each individual is then swapped twice (to make sure it is really random) with the condition assignment of a randomly chosen participant. Half of the participants (15 individuals) will perform the experimental condition first, while the other half will perform the control condition first. The sequence, and with it the assignment to the first intervention condition, is hidden from the researcher that enrolls the participants until the intervention starts to avoid biases; once the intervention begins, the sequence is no longer blinded from anyone.

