#### Stroop task

To measure the actual efficacy of the proposed intervention, we will record cortical hemodynamic changes in the participant’s PFC using the functional near-infrared spectroscopy (fNIRS) device before and after every IVR session (either 1PP and 3PP) during the execution of the color-word matching Stroop task (see Fig. 2 a).

We will adopt the Stroop task as previously used in several studies [17, 22, 46–48]. The Stroop task we plan to use consists of 30 trials, including 10 neutrals, 10 congruent, and 10 incongruent, presented in random order. For all trials, two words are displayed on the monitor one above the other: specifically for neutral trials, the upper row consists of XXXX printed in red, white, blue, pink, or yellow, and the lower row shows the words “RED,” “WHITE,” “BLUE,” “PINK,” or “YELLOW” printed in black. For congruent trials, the upper row contains the words “RED,” “WHITE,” “BLUE,” “PINK,” or “YELLOW” printed in the congruent color (e.g. RED was printed in red) and the lower row contains the same color words printed in black. For incongruent trials, the color word in the upper row is printed in an incongruent color (e.g. RED was printed in yellow) to produce cognitive interference between the color word and the color name (i.e. Stroop interference). All words were written in Japanese (hiragana). The lower row is presented 100 ms later than the upper row, in order to achieve sequential visual attention. Between each trial a fixation cross is shown, as an inter-stimulus interval, for 9–13 s to avoid timing prediction [17, 22, 49]. The stimulus remains on the screen for 2 s, independently from the participant’s answer. We will train participants to decide whether the color of the upper word (or letters) corresponds to the color name of the lower word by pressing button 1 on the keypad to give “yes” responses or button 2 to give “no” responses with their forefingers. Of the presented stimuli, 50% were correct (the correct answer is “yes”). We recorded response time (RT) and error rate (ER) as variable.

The Stroop task will be administered entirely via computer (to avoid biases due to presence of the researcher, especially concerning RT); for the present study, the Stroop task has been implemented using E-prime 2.0.

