### Statistical analysis

The current RCT is designed to determine whether a virtual intervention has a beneficial effect on executive functions; this is possible only if some assumptions, during the intervention itself, are satisfied (e.g. embodiment over the virtual body in 1PP). Consequently, the data analysis will be organized in two phases: in the first phase, the results collected during the intervention itself will be checked (i.e. HR, online and offline questionnaires) in order to see whether the virtual intervention is actually effective. In the second phase, the measurements will be analyzed to check the hypothesis (i.e. Stroop task and fNIRS data) and their correlations.

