## Discussion

The background of this RCT protocol study starts with two assumptions, based on data presented in the literature: (1) HIE has acute beneficial consequences on executive functions and their neural basis [17, 67]; and (2) the movements of their own virtual body can generate measurable consequences on their real body, comparable to the ones when we actually move [33, 41].

Consequently, we hypothesized that the same HIE intervention performed by their own virtual body (and not by the real participants’ bodies) can have the same beneficial acute effects on executive functions.

In order to confirm our hypothesis, 30 healthy young adults will undergo a vHIE, where the virtual body exclusively (the real body is still sitting) will perform 8 min of training, alternating 30 s of running and 30 s of slow walking; the same vHIE will be performed in two intervention conditions: 1PP, the virtual body will be displayed with the real one, spatially replacing it, and so it will be considered as their own; in 3PP, the virtual body will be displayed 1.5 m away on the right side of the real one, and so it will simply be considered as someone else. During the vHIE, we will record the HR: we predict finding a fluctuating trend of the HR during the intervention in 1PP (and not in 3PP), coherent with the virtual movements, as if the individual is actually performing them. In addition, we will ask the participants to report verbally any subjective feelings during the intervention, predicting that increased sensations of SoBO and SoA in 1PP respect to 3PP will be found.

To test our main hypothesis about acute beneficial effects on executive functions, before and after the two vHIE intervention conditions, we will record the participants’ performance of the Stroop task; at the same time, we will record cortical hemodynamic changes over the PFC with the fNIRS. We predict finding better performance, in terms of reaction time and accuracy, in the Stroop task and higher activation of the neural correlated areas (i.e. PFC) after the vHIE in 1PP (and not after 3PP).

If we confirm our hypothesis, it means that virtual training performed only with the own virtual body can raise the same physical but especially cognitive and neural consequences of a “real” physical one.

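### The online ownership and agency items are spoken live while nobody is masked, so delivery could inflate the 1PP versus 3PP contrast in this one of three parts of the embodiment check

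*Protocol article*

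**What the plan says.** **Mode.** Online and offline questionnaires on SoBO and SoA, in the note to Table 1, describes the online form as "Questionnaire verbally administered during the vHIE". The same section says "we will ask participants to rate their level of agreement" on a scale of 1 to 7 for four statements: ownership (s1), ownership control (s2), agency (s3) and agency control (s4). The Discussion indicates that the answers are spoken too: "we will ask the participants to report verbally any subjective feelings during the intervention". The five timepoints are 2 min into the baseline, then 1, 2.5, 5 and 6.5 min into the virtual exercise.

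**Masking.** Randomization of interventions conceals the sequence until the intervention starts, but "once the intervention begins, the sequence is no longer blinded from anyone".

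**Stroop task.** This is run entirely by computer, "to avoid biases due to presence of the researcher, especially concerning RT".

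**Use of the ratings.** Statistical analysis makes embodiment in 1PP a precondition for answering the main question. In the first phase, "the results collected during the intervention itself will be checked (i.e. HR, online and offline questionnaires"). The section on the questionnaire data predicts that the real statements will score higher in 1PP than the control statements do, and higher than in 3PP.

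**The other two components.** The offline form is described as "Questionnaire self-administered after the vHIE interventions concerning the subjective participant’s feelings during the previous intervention", with its domain labels "not shown to the participant". It covers ownership (s6), agency (s9) and ownership control (s10). Heart rate is recorded by a chest-worn monitor.

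**The concern.** A spoken rating of a feeling, given to someone who knows the condition and the expected result, can be affected by how the question is put. The asker may stress a statement, pause, repeat it or respond to an answer differently in 1PP and 3PP. Any such difference is likely to favour the study's own prediction. It would then be mixed with the illusion in the online ratings, and those ratings alone could not tell the two apart.

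The protocol accepts that a researcher's presence can bias a measurement and automates the Stroop task for that reason, but it describes no similar protection for the online ratings. At stake is how far the online 1PP versus 3PP contrast can be trusted as evidence that 1PP induced ownership and agency, and hence how a Stroop difference would be interpreted.

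**Working it through.** **1. Is the asker masked?** The items are spoken during the session, and masking ends for everyone when the intervention begins. The article does not say which researcher asks. That the asker knows the condition is an inference, but the masking statement leaves nobody masked who could do it.

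**2. How much is exposed?** 4 statements × 5 timepoints × 2 sessions = 40 spoken ratings per participant.

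**3. Timing.** With 30 s of running followed by 30 s of slow walking, running starts at 0, 1, 2, … min and walking at 0.5, 1.5, 2.5, … min. The prompts at 1 and 5 min fall at the start of a running phase, and those at 2.5 and 6.5 min at the start of a walking phase. This agrees with the protocol's labels. Four statements and four answers must fit into 30 s for every rating to belong to the named speed. The protocol fixes the start times. Live speech does not fix the pace after that.

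**4. Which parts of the embodiment check are exposed?**

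| Component | How collected | Exposure to live delivery |
|---|---|---|
| Online form, s1 to s4 | spoken, nobody masked | direct |
| Offline form, incl. s6, s9, s10 | self-administered, domain labels hidden | indirect: follows the spoken rounds, with similar items |
| Heart rate | chest monitor | least: not a rating |

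Only the first row is directly open to the asker's delivery.

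**5. Do the control statements protect the online contrast?** Partly. A general tendency to agree would raise s2 and s4 as well as s1 and s3, and the planned 4 × 2 ANOVA of statement by condition would help to show it. But s2 is close to the reverse of s1, so a prompt that favours ownership could raise s1 and lower s2, which widens the predicted difference.

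**6. Illustration of size.** The protocol gives neither an SD for the ratings nor any prompting effect, so both are assumed. Take a single paired 1PP minus 3PP difference, n = 30, two-sided 5%, and no true effect. With a shift b and SD s of the paired difference, d = b/s, the noncentrality is d√30, there are 29 degrees of freedom and the critical t is 2.045.

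| Shift b (points) | SD s | d | d√30 | Chance of significance |
|---|---|---|---|---|
| 0.5 | 1 | 0.500 | 2.739 | 75% |
| 0.5 | 1.5 | 0.333 | 1.826 | 42% |
| 0.5 | 2 | 0.250 | 1.369 | 26% |
| 0.25 | 1 | 0.250 | 1.369 | 26% |
| 0.25 | 1.5 | 0.167 | 0.913 | 14% |
| 0.25 | 2 | 0.125 | 0.685 | 10% |

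The reference is 5% with no shift. This models one paired difference, not the planned 4 × 2 ANOVA. It shows what an assumed bias would do if it existed and is no evidence that one exists. The planned sample size of 28 (30 recruited) is for Stroop response time and does not depend on how the questionnaire is given.

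**The case against.** The strongest reply is that two of the three components do not pass through the asker. If prompting inflated the spoken ratings, the offline form or heart rate could disagree and expose it. This stands, and it limits the point. A reader might infer that prompting could create the whole embodiment check, or that the design cannot separate prompting from the illusion. The documents support neither reading. The offline form is less exposed rather than immune, because it comes right after the spoken rounds. Heart rate is a real safeguard, though it cannot show that the ratings themselves are unbiased.

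A reader might also infer that the protocol removed the researcher from the Stroop task to avoid this same bias. It did not say so. The stated reason is the researcher's presence, chiefly for response time, and not prompting of subjective ratings. The contrast shows awareness of a related problem and is not a contradiction.

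Other replies hold in part:
- The questionnaires are additional outcomes, and the primary outcome is computerised. A biased rating cannot produce a Stroop difference; it can only affect how one is interpreted.
- No passage says that tone, wording or pace will vary, and an article may leave the script to the full protocol. But spoken delivery without masking is a stated choice, and a better one is readily available.
- The shifts and SDs are assumed. At SD 1.5, even a 0.5-point shift misses significance more often than not.
- Participants wear a visor and must keep still, so spoken answers are practical. The fix keeps them.

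**Conclusion.** The concern holds for the online questionnaire only. The s1 to s4 ratings are given live when nobody is masked, so their 1PP versus 3PP contrast could be inflated by differences in delivery, in the predicted direction. This weakens one of three components of the embodiment check; the other two are less exposed.

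Its size cannot be derived from the documents. The 42% (26% to 75%) for a 0.5-point shift and 14% (10% to 26%) for a 0.25-point shift are illustrations under an assumed SD of 1.5 (range 1 to 2) and a simplified test. The conclusion rests on one strong inference, that whoever asks the items knows the condition. It is worth correcting because the remedy is cheap.

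**What to change.** In the section on the online questionnaire, state that the existing virtual-reality program plays the four statements as one fixed recording, with the same voice, wording and programmed times in both conditions. The participant says only the number and the researcher stays silent. Audio-recording the answers would allow them to be checked. A fixed recording also makes the pace of the prompts within each 30 s phase the same in 1PP and 3PP.

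State as well that the online ratings will be read alongside the offline form and heart rate. The recording removes variation from the prompter but not participants' own expectations, since they can see the perspective.

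The cost is a short recording and a small script in the existing program, with no extra staff or visits.
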